### Covariate classification

It is recognised that some patients may remain in the cohort for a long time and their covariates may change. Therefore, covariates will be identified separately for each of the time periods the patient contributes data and will be grouped by DOAC, warfarin or no OAC, depending on exposure for that period.

We want to investigate whether certain comorbidities influence the prescribing of OACs. We will therefore look for comorbidities accumulated up to the end of the time period for patients who do not receive an OAC or the OAC index date where one is prescribed. Patients will be classified as having a comorbidity if the patient record contains ≥1 diagnostic Read code for a disease or ≥3 Read codes supporting the presence of the disease at any time prior to the relevant date for that period. Read codes used to support the presence of disease include attendance at specialist clinics (eg, diabetes clinics) or codes related to follow-up, such as hypertension monitoring.

Concomitant medication will be classified as≥1 prescription issues for a medication of interest in the 3 months prior to study entry, commencing an OAC, or the end of the time period. We will describe medications at study entry as baseline and then in each time period for the no OAC and incident OAC patients as described for the comorbidities previously mentioned. The medications of interest affect either stroke or bleeding risk or commonly interact with OACs (antihypertensives, antiplatelets, statins, diabetic medications, antiarrhythmics, non-steroidal anti-inflammatory drugs, corticosteroids, anticonvulsants, systemic azoles, HIV protease inhibitors and ciclosporin).

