#### ​Incident and prevalent users

Exposure status will be defined at cohort entry as

‘No OAC’, where the patient had at least a year free of OAC prior to study entry and does not receive an OAC during the study period.‘Incident OAC users’, where the patient had at least a year free of OAC prior to study entry then was prescribed an OAC during the study period.‘Prevalent OAC users’ if the patient received an OAC in the year prior to study entry.

Exposure status for incident OAC users will be stratified at the start of each study period to no OAC, warfarin or DOAC.

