#### ​Heart valve replacements and mitral stenosis

Historically, AF patients have been classed as having valvular or non-valvular AF, but definitions of these have varied.^22^ The licensing for DOACs in the UK states they should only be prescribed for patients with non-valvular AF, however, the randomised controlled trials for the DOACs all defined valvular AF differently and exclusion criteria varied.^23^ Recently updated European Society of Cardiology guidelines suggest that VKAs should be the preferred option for patients with mechanical heart valves or moderate to severe mitral stenosis.^4^ This co-variate has been included to investigate what proportion on DOAC and warfarin users have a history of mechanical heart valves or Read codes for moderate or severe mitral stenosis.

#### 
*​*Number of general practice encounters

The number of encounters with healthcare professionals from general practice in the year prior to study entry, the year preceding the OAC index date or preceding the end of the time period will be used as an indicator of healthcare use.

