#### ​Objective 2: to describe switching between OACs during the study period

The number and percentage of patients switching from warfarin to DOAC, DOAC to DOAC and DOAC to warfarin will be calculated. The number of patients with multiple switches and details of the switches will be described. The average time to switch will be reported.

#### 
*​*Objective 3: to compare the characteristics of patients with AF who were newly started on OACs during each period described in objective 1, to those who were not prescribed anticoagulation in the same period

Demographics, characteristics, comorbidities and concomitant medications will be reported for the three time periods described. Prevalent OAC users will be excluded from this part of the study as we want to compare those started on an OAC with those who are not during each time period.

Patients may contribute data to more than one group, but they will be censored at the time they are prescribed their index OAC. For example, they may enter the study during the first time period but may not be prescribed an OAC until period 3. In this case, they would contribute data to the no-OAC group in time periods 1 and 2 and then one of the OAC groups in period 3. If they entered in period 1 and started on an OAC in period 2, they would contribute data to the no OAC group in period 1 and the OAC group in period 2; they would not contribute any data to period 3 as they would be censored. Figure 3 illustrates how patients contribute to different groups during their time in the study. Patient demographics (age and biological sex) and characteristics (BMI, smoking status and alcohol consumption) will be reported as percentages in predefined categories. The proportion of the cohort with each of the comorbidities and concomitant medications will be described. The mean CHA_2_DS_2_-VASc and HAS-BLED scores will be reported.

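### Objective 3 reads covariates at period end for untreated patients but at the OAC index date for starters, so untreated patients look sicker even with no true difference

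*Protocol article*

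**What the plan says.** Covariate classification sets two reading dates, one for the untreated and one for starters: it looks for "comorbidities accumulated up to the end of the time period for patients who do not receive an OAC or the OAC index date" for patients who are prescribed one. A code counts if recorded "at any time prior to the relevant date for that period", so the look-back has no lower limit.

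The same pair of dates recurs elsewhere:
- Concomitant medication is a prescription "in the 3 months prior to study entry, commencing an OAC, or the end of the time period".
- Practice encounters are counted over a year, and after the study-entry count "the year preceding the OAC index date or preceding the end of the time period will be used".
- Renal impairment uses the code or test nearest to the relevant date for the period.

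Under Statistical analysis, Objective 3 compares these groups within each period, excludes prevalent users and censors starters at their index OAC. A patient first treated in period 3 is an untreated patient before that: "they would contribute data to the no-OAC group in time periods 1 and 2". The stated reason for collecting comorbidities is to see whether they influence OAC prescribing. The limitations in the Discussion do not mention the reading date.

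**The concern.** An untreated patient goes on collecting diagnoses, bleeds, falls, fractures and score points until the period closes. A starter stops collecting on the day of the first OAC. Part of any difference between the groups is therefore a difference in how long each was watched.

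The order of events also suffers. A diagnosis made in year 4 cannot have shaped a decision not to anticoagulate in years 1 to 3. A stroke during untreated time adds 2 points to CHA2DS2-VASc and 1 to HAS-BLED, so a possible consequence of non-treatment is tabulated as a characteristic preceding it. If comorbidity really prompts treatment, this artefact works against that pattern and could hide or reverse it. The planned 95% confidence intervals do not help, because the error is bias and not sampling variation.

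**Working it through.** **Inputs from the protocol.** The reading dates and look-back quoted above; three periods of about 5 years each (the last ends on 27 December 2017, 4.99 years). The protocol states no onset, initiation or exit rate and no sample size, so there is no figure to reproduce.

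**Assumed inputs.** Prevalence at entry 20%; onset c of 2, 5 or 10% per year; OAC initiation λ of 10% per year (20% in one scenario); exit 0 to 20% per year; 0 to 100% of patients entering during the period. In some scenarios 30% of those new entrants start early (mean 0.25 years). Initiation and exit are independent of comorbidity, so any gap comes from the reading date alone. Untreated patients are read at period end, or at exit if earlier. For a cumulative look-back these are the same, since no codes accrue after exit.

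**Simplest case in closed form** (all present at period start, no exits):
- Untreated prevalence = 1 − 0.8·exp(−5c). At c = 0.05: 1 − 0.8 × 0.7788 = 37.7%.
- Starters' prevalence = 1 − 0.8·[λ/(λ+c)]·[1 − exp(−5(λ+c))]/[1 − exp(−5λ)]. At λ = 0.10, c = 0.05: 1 − 0.8 × 0.6667 × 0.5276/0.3935 = 28.5%.
- Starters' mean reading time = 1/λ − 5·exp(−5λ)/[1 − exp(−5λ)] = 10 − 5 × 0.6065/0.3935 = 2.3 years, against 5.0 years for the untreated.

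**Simulation** (2,000,000 patients per scenario, one 5-year period). Each pair is starters vs untreated. Gaps and odds ratios (OR) were computed before rounding.

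| Scenario | Onset per year | Mean reading time (years) | Prevalence (%) | Gap (points) | OR |
|---|---|---|---|---|---|
| All present at start, no exits | 2% | 2.3 vs 5.0 | 23.5 vs 27.6 | 4.1 | 1.24 |
| Same | 5% | 2.3 vs 5.0 | 28.5 vs 37.7 | 9.3 | 1.52 |
| Same | 10% | 2.3 vs 5.0 | 35.7 vs 51.5 | 15.7 | 1.91 |
| 12% exits, all present at start | 5% | 2.0 vs 3.5 | 27.7 vs 32.5 | 4.8 | 1.25 |
| 12% exits, half enter mid-period | 5% | 1.8 vs 2.6 | 26.7 vs 29.4 | 2.7 | 1.14 |
| Same, 30% of new entrants start early | 2% | 1.2 vs 2.7 | 21.9 vs 24.2 | 2.3 | 1.14 |
| Same | 5% | 1.2 vs 2.7 | 24.6 vs 29.8 | 5.2 | 1.30 |
| Same | 10% | 1.2 vs 2.7 | 28.5 vs 38.0 | 9.4 | 1.53 |
| 20% initiation, 20% exits, half mid-period, 30% early | 5% | 1.2 vs 2.0 | 24.3 vs 27.3 | 3.0 | 1.17 |
| 20% exits, all enter mid-period | 5% | 1.3 vs 1.7 | 24.9 vs 26.2 | 1.3 | 1.07 |

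**Visibility.** With an assumed 5,000 patients per group, z = gap / √[(p₁(1−p₁) + p₀(1−p₀))/5000]. For the 24.6 vs 29.8 row this is 0.052/0.0089 = 5.9. It is 1.5 in the mildest row and 2.7 to 16.1 in the others, so a 95% interval would usually exclude no difference.

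**Scores.** A false gap d in an item worth w points adds w × d to the gap in mean score. At 5.2 points, a one-point item adds 0.052 and a two-point item 0.104.

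**With a comparable date.** In the same simulations, reading both groups at entry gives 20% in each. Reading each starter against a not-yet-treated patient at the same time since entry agrees within 0.3 points in every scenario.

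**The case against.** Objective 3 is descriptive: percentages and mean scores, with no test or model. Medication and encounters are also described at study entry, which is a common anchor. Both points are true. But the study-entry description does not extend to comorbidities or scores, and the protocol itself gives influence on prescribing as the purpose, so the descriptive label does not remove the problem.

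Size is the better objection. The largest gaps assume that everyone is present at period start and nobody leaves, which is unrealistic at age 75 and over. Exits and staggered entry shrink the gap, to 1.3 points in the mildest scenario. That stands, and the upper figures should be read as an upper end.

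Three stronger readings are tempting and are not supported:
- **Empty windows after death.** A reader might infer that untreated patients who die early are read in a window falling after death and so appear unmedicated. With assumed mortality of 8 to 15% per year, 1 − exp(−4.75m) gives 32 to 51% dying more than 3 months before period end. But the protocol censors at death or departure and does not say that windows run beyond it. It simply names no date for these patients.
- **Contradictory group membership.** Under Incident and prevalent users, a no-OAC patient is one who "does not receive an OAC during the study period", which seems to clash with the Objective 3 example. That section closes, however, by stratifying status at the start of each period, and Time periods lets patients contribute to more than one group. The matter is one of wording.
- **Distorted covariates in Objective 4.** That analysis includes only incident users, all read at the index date. It is affected only through the choice of covariates identified in Objective 3.

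**Conclusion.** The concern holds for covariates read cumulatively: comorbidities, bleeds, falls, fractures and both risk scores. Followed exactly, the rule makes untreated patients look sicker with no true association, and nothing else in the protocol corrects it. The direction was the same in every scenario. The size rests wholly on assumed rates: about 1 to 16 points (odds ratio about 1.07 to 1.9), and about 5 points (odds ratio 1.3) at 5% annual onset with exits, mid-period entry and some early starts. Exit was taken as independent of comorbidity, which real data may not respect.

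Renal impairment, medication and encounters share the unequal anchor. For the fixed windows (3 months and 1 year) the bias may go either way, and the date for untreated patients who die or leave early is undefined. Sex is unaffected, and DOAC-versus-warfarin contrasts among starters share one anchor. Because the flaw bears on Objective 3's central comparison, it should be corrected before that analysis is run.

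**What to change.** In Covariate classification, Renal impairment and Number of general practice encounters, replace the period-end date with a reference date comparable between groups. Either option works:
1. For everyone, the later of period start and cohort entry.
2. For starters the OAC index date, and for each untreated patient a risk-set or pseudo-index date at the same time since entry, while alive, registered and untreated.

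Read all covariates and scores on or before that date. Tie the HAS-BLED drug item to it as well; at present that item is scored on any prescription within the period. Keep the period-end reading at most as a secondary description. Either option also supplies the missing date for untreated patients who die or leave early. Under Incident and prevalent users, state that the Objective 3 no-OAC group is specific to each period.

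The cost is protocol wording and modest reprogramming on data already held. Option 1 is simpler but misses conditions that arise between entry and a later OAC start. Option 2 captures them but needs a fixed seed if dates are drawn at random.

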### Time periods

The cohort will be analysed in three time periods:

Period 1: prior to the introduction of DOACs (2003–2007).Period 2: during the period between the introduction of DOACs and the time they were recommended by NICE (2008–2012).Period 3: following the publication of the NICE technology appraisals recommending DOACs as an option for stroke prevention in AF (2013–2017).

For each time period, patients will contribute data to either the warfarin, DOAC or no OAC group. Patients in the cohort can contribute data to more than one time period and more than one group, and may contribute differently for each objective. Patients may only contribute to the incident OAC group once with their index OAC. Any further prescriptions for different OACs would be considered to be prevalent.

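### In Objective 3, covariates are read at period end for untreated patients but at OAC start for starters, which biases comorbidity prevalence and risk scores upward in the no-OAC group

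*Protocol article*

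**What the plan says.** The Covariate classification section gives the aim: "We want to investigate whether certain comorbidities influence the prescribing of OACs". It then fixes the reading date by group, counting "comorbidities accumulated up to the end of the time period for patients who do not receive an OAC or the OAC index date" for starters. The look-back is cumulative, since a qualifying code counts "at any time prior to the relevant date for that period". The CHA2DS2-VASc and HAS-BLED elements for stroke, bleeding, hypertension, heart failure and so on are comorbidity histories of this kind, so their reading date follows the same rule.

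Concomitant medication is defined by a prescription "in the 3 months prior to study entry, commencing an OAC, or the end of the time period". The subsection on general practice encounters also uses index date or end of period: "the year preceding the OAC index date or preceding the end of the time period will be used as an indicator of healthcare use". For these two items a study-entry reading is planned as well. For medications the article says "We will describe medications at study entry as baseline", and encounters are also counted in the year before study entry. No such entry reading is stated for comorbidities or scores.

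Under Objective 3 in Statistical analysis, new starters are compared with patients not anticoagulated in the same period (2003–2007, 2008–2012 or 2013–2017). The output is given as "The proportion of the cohort with each of the comorbidities and concomitant medications will be described", together with mean scores. Objective 4 then adjusts its Cox model for age and for covariates found important in Objective 3. The limitations in the Discussion do not mention the unequal dates.

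**The concern.** To learn whether a comorbidity influences prescribing, one needs its status when the decision was made, compared with the status of untreated patients at a similar point. Here a starter's history stops at the index date, while an untreated patient's history runs on to the end of a period of up to five years. With a cumulative look-back, moving the date later can only add diagnoses. Untreated patients therefore have more time to acquire dementia, falls, bleeds and score points for reasons unrelated to the prescribing decision. A code recorded in year 4 cannot explain non-treatment in years 1 to 3. A stroke while untreated, with no OAC start before period end, adds 2 CHA2DS2-VASc points and 1 HAS-BLED point to the no-OAC mean.

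At stake is the interpretation of the main Objective 3 contrast. A comorbidity with no influence could be reported as a reason for withholding anticoagulation. A large cohort would give a narrow confidence interval around that artefact. For medications (3-month window) and encounters (1-year window) the look-back is not cumulative, so the dates are not comparable but the direction of the effect is not forced.

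**Working it through.** The article states no figure on this point, so there is nothing to reproduce. The check asks what difference the rule creates when OAC start is unrelated to the comorbidity.

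**From the article:** 5-year periods; starters read at index; no-OAC patients read at period end; cumulative look-back.

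**Assumed:** half the patients are present at period start and the rest enter uniformly over the period; prevalence at entry is 20% in everyone; start hazard h(t), exit rate μ and new-onset rate a are independent of each other. A no-OAC patient who exits early is read at exit, which is the mildest reading of the rule.

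**Formula.** Let L be the time from entry to period end and S(t) = exp(−∫h − μt).
- Starters free of new onset when read: ∫h·S·e^(−at)dt ÷ ∫h·S dt, over 0 to L.
- No-OAC patients free of new onset when read: [∫μ·S·e^(−at)dt + S(L)·e^(−aL)] ÷ [∫μ·S dt + S(L)].
- Numerators and denominators are averaged over entry times. Prevalence when read = 1 − 0.8 × (fraction free).

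**Case that can be done by hand:** patients present at period start, h = 0.10, μ = 0.10, a = 0.05, L = 5.
- Start within the period: 0.5 × (1 − e^(−1)) = 0.316. Exit untreated: 0.316. Reach period end untreated: e^(−1) = 0.368.
- With constant hazards, starters and early exits have the same mean reading time: 5 − 5 × 0.368/0.632 = 2.09 years. Patients who reach period end are read at 5 years. The no-OAC mean is (0.316 × 2.09 + 0.368 × 5)/0.684 = 3.66 years, about 1.57 years later than starters.
- Fraction free, starters: (0.2/0.25) × (1 − e^(−1.25))/(1 − e^(−1)) = 0.903, so prevalence is 1 − 0.8 × 0.903 = 27.8%.
- Fraction free, no OAC: (0.316 × 0.903 + 0.368 × 0.779)/0.684 = 0.836, so prevalence is 1 − 0.8 × 0.836 = 33.1%.
- The false excess is 5.3 points, and it comes entirely from patients carried to period end.

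Adding the half who enter during the period shrinks the gap: 26.9% in starters against 29.9% with no OAC (+3.0 points), with reading dates 0.88 years apart.

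**Range, exit 12% per year, all entrants:**

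| Initiation | No-OAC read later by | False excess, onset 2% to 10%/yr |
|---|---|---|
| 10%/yr constant | 0.8 yr | 1.2 to 4.8 points |
| 20%/yr constant | 0.7 yr | 1.0 to 4.0 points |
| Hazard 1/yr for 6 months, then 5%/yr | 2.1 yr | 3.3 to 13.9 points |
| Hazard 1/yr for 6 months, then 10%/yr | 1.8 yr | 2.8 to 11.7 points |

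A separate simulation of 30 scenarios (exit 0–20% per year, onset 2–5% per year) gave a false excess in every one: 0.7 to 5.3 points with constant initiation and 2.6 to 9.5 with front-loaded initiation. With both groups read at entry the difference was zero within simulation noise (±0.2 points).

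**When the event itself prompts treatment.** With new strokes at 3% per year, and start and exit both 10% per year, the share with a new stroke before the reading date is:

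| Strokes prompting an immediate start | No OAC | Starters |
|---|---|---|
| 0% | 7.7% | 5.3% |
| 10% | 7.0% | 7.4% |
| 25% | 5.9% | 10.5% |

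For such an event the rule still adds to the no-OAC group, but the observed contrast can reverse.

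**The case against.** The strongest defence is that non-treatment continues throughout the period. A bleed or dementia diagnosis in year 3 can be a genuine reason for remaining untreated, and the article re-reads covariates each period because they change. Objective 3 reports proportions and means, with no causal model. This has force, but it argues for comparing starters and untreated patients at the same point in follow-up. Period end is only the last moment of a continuing decision, and the section's stated aim is influence on prescribing.

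Four stronger readings are tempting, and the documents do not support them.
- *The no-OAC group will look older.* No section dates the reading of age, so this follows only if age is read on the same date. Age cannot raise the scores either: everyone is at least 75, so it contributes a constant 2 points to CHA2DS2-VASc and 1 to HAS-BLED.
- *The no-OAC group will look sicker on every item.* Events that prompt an OAC start count with the starters, and the stroke figures above show that this can reverse the contrast.
- *The Objective 4 hazard ratios are biased.* That model contains only incident users, whose covariates are all read at the index date. Only the choice of covariates could be affected.
- *No common-date reading is planned at all.* One exists for medications and encounters, but not for comorbidities or scores.

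The size depends on rates the article does not give. The upper end needs both early initiation and onset of 10% per year for a single comorbidity.

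**Conclusion.** The point holds as a directional bias. Unequal reading dates with a cumulative look-back raise comorbidity prevalence and mean scores in the no-OAC group relative to starters, for reasons unrelated to prescribing, and nothing else in the article corrects this. Under the assumed rates the artefact is about 1–5 percentage points with constant initiation and about 3–14 with front-loaded initiation, from equal prevalence at entry. These figures assume that initiation is independent of the comorbidity and that patients who leave early are read at exit. The sign of any particular observed difference cannot be predicted from the rule alone. Objectives 1 and 2 are unaffected, and Objective 4 is touched only through covariate selection. The rule should be changed, but it does not undermine the study as a whole.

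**What to change.** In Covariate classification, Number of general practice encounters, and Objective 3 of the Statistical analysis, make the primary comparison at a comparable date in both groups, for comorbidities, both scores, medications and encounters. There are two workable options.

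1. Read everyone at the later of period start and cohort entry. This extends to comorbidities and scores the kind of entry reading already planned for medications and encounters. Its cost is that it misses later events that triggered prescribing, and values are older for patients who start late in a period.
2. For each starter, take patients still untreated and in follow-up on that index date, in the same period and with similar time since cohort entry, and read both at that date. This keeps triggering events. Its cost is that patients who start later in the period can serve as comparators before they start, so the comparator wording in Objective 3 (not anticoagulated in the same period) must be adjusted.

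Whichever is chosen, state the date at which age is read, and keep the current index-date and end-of-period reading as a secondary description with its limitation noted. Either option needs protocol wording and programming on data already held.

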### Source population

The study period will start on 1 January 2003 and will end on 27 December 2017. The source population will consist of all patients in CPRD who have ≥1 Read codes for AF and have contributed a minimum of 12 months’ research standard data prior to entry into the cohort. To be eligible to join the study, patients need to have the following: a Read code for AF recorded during or any time prior to the start of the study period; evidence to support the diagnosis of AF, such as a second AF diagnosis at a later date, an echocardiogram or prescription for a rate limiting or antiarrhythmic medication in the 3 months before the AF diagnosis or anytime after; and age of ≥75 years at study entry.

Patients will enter the cohort at the latest of the following dates:

Start of the study period.First AF diagnosis.75th birthday.A year from the date they started to contribute research standard data.

Patients will be censored if they leave the practice, the practice stops contributing data, at their date of death or at the end of the study. For the incidence calculations and comparison of patient characteristics, patients will be censored when they are prescribed an OAC.

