##### Acute kidney injury

Previous episodes of acute kidney injury may influence the decision to prescribe an anticoagulant and which anticoagulant to prescribe. Read codes for acute kidney injury will be counted as discrete events where they occur ≥1 week apart.

#### 
*​*Hepatic disease

Hepatic disease is an independent risk factor for bleeding and also affects the metabolism of warfarin, so it may affect the decision to prescribe anticoagulation. Hepatic disease will be defined as specified under the HAS-BLED section.

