## Discussion

A number of studies have described changes in anticoagulation prescribing in the time since DOACs were introduced in the UK.^15 27 28^ However, none have focused specifically on their use in older people aged ≥75 years, despite older people being the largest users of anticoagulants for AF. The main strength of this study is that it will investigate prescribing in a large cohort of older patients using the CPRD, which is generally representative of the UK population. This study will look at a number of different factors that may influence the prescribing of anticoagulants and how these have changed over time. The results of this study will inform future comparative studies between OACs as it will provide an insight to potential confounders which may need to be controlled for. A limitation of this study is defining accurately when patients are exposed to an anticoagulant and when they are not. This is particularly difficult for warfarin as dosing information is not included in the CPRD. A number of studies have compared DOACs and warfarin using routinely collected healthcare data, but they do not describe how they mapped warfarin exposure.^29 30^ This protocol is transparent in describing our planned method for warfarin mapping and uses both prescription and test result data. We will also investigate gaps in prescribing to establish whether patients may have been in the hospital or having their OAC prescribed elsewhere; this is likely to be more common in this age group than others and has been noted as a limitation in other studies.^31^ A second limitation is that comorbidities may not always be recorded in the CPRD, particularly where they are diagnosed and treated in secondary care. However, as the comorbidities we have chosen are chronic and likely to have a significant impact on patients’ health, it is likely that they would be recorded accurately. Finally, as it is difficult to predict whether prescriptions for concomitant medicines are still continuing at any given time, we have decided to assume that if a prescription was issued in the 3 months prior to an OAC being started, the concomitant medicine is still continuing at that time. This is likely to be the case as most medications of interest are for chronic conditions. However, we acknowledge that it may overestimate exposure to these concomitant medications.

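### Open-ended look-back for falls, bleeds, fractures and acute kidney injury can create apparent differences between periods or groups that reflect record length

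*Protocol article*

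**What the plan says.** Under Covariate classification, comorbidities are re-identified for each period in which a patient contributes. The plan takes "comorbidities accumulated up to the end of the time period for patients who do not receive an OAC or the OAC index date" for those who start treatment. A condition counts if there is one diagnostic code or "≥3 Read codes supporting the presence of the disease at any time prior to the relevant date for that period".

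The definitions of previous bleed, falls and fragility fractures add no time window. For acute kidney injury, "Read codes for acute kidney injury will be counted as discrete events where they occur ≥1 week apart", again with no limit on how far back.

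On the length of record, Source population requires only that patients "have contributed a minimum of 12 months’ research standard data prior to entry into the cohort". No maximum or distribution is given. Under Time periods, "Patients in the cohort can contribute data to more than one time period and more than one group". The analysis text for objective 3 gives the example of a patient first treated in period 3: "they would contribute data to the no-OAC group in time periods 1 and 2 and then one of the OAC groups in period 3".

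The Discussion says the study will look at "different factors that may influence the prescribing of anticoagulants and how these have changed over time".

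**The concern.** For an item defined as ever coded, the chance of being positive rises with the length of record searched. Re-reading covariates in each period moves the end of the look-back but does not equalise its length. If records are typically longer in 2013–2017 than in 2003–2007, falls, bleeds, fractures and kidney injury can look more common with no change in the patients. If one group has more patients with short records, its events are captured less fully within a period.

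The Introduction names falls risk and previous bleeding among the reasons physicians give for withholding vitamin K antagonists. A rise in these items among patients started on treatment after 2012 would invite the reading that direct oral anticoagulants (DOACs) opened treatment to frailer patients. As planned, a reader could not tell that from longer records. The covariates from objective 3 also feed the adjustment of the Cox model in objective 4, and the Discussion offers them as candidate confounders for later studies.

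**Working it through.** The article gives no prevalence, coding rate or record-start date, so there is no figure to reproduce. What follows is illustration.

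**Inputs from the article:** period ends at the close of 2007, 2012 and 2017; a 12-month minimum record before entry; no upper limit on look-back.

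**Assumptions:** a constant yearly rate of first code, r = 0.03 (other rates where stated), and the record starts named below.

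**Formula:** ever-coded share = 1 − exp(−r × L), with L the look-back in years.

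**1. Spread at one date.** A patient entering on 1 January 2003 with the minimum record has about 6, 11 and 16 years at the three period ends. The shares are 1 − exp(−0.18) = 16.5%, 1 − exp(−0.33) = 28.1% and 1 − exp(−0.48) = 38.1%. A new entrant with about 1 year has 1 − exp(−0.03) = 3.0%. The rise along the first patient's own line is mostly real accumulation. The gap of 38.1% against 3.0% between two patients with the same underlying rate, read on the same date, is record length.

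**2. Common record start.** If all records start in 1995, L = 13, 18 and 23, giving 32.3%, 41.7% and 49.8% with no change in the rate. If half the patients have such records and half always have 3 years (1 − exp(−0.09) = 8.6%):
- Period 1: 0.5 × 8.6 + 0.5 × 32.3 = 20.5%
- Period 2: 0.5 × 8.6 + 0.5 × 41.7 = 25.2%
- Period 3: 0.5 × 8.6 + 0.5 × 49.8 = 29.2%

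For acute kidney injury the item is a count. At a constant episode rate it grows in proportion to L, so going from 13 to 23 years multiplies it by 23/13 = 1.77.

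**3. Open cohort.** A simulation allowed entry, exit (12% per year) and removal at the start of an oral anticoagulant (OAC; 8% per year). Ever-coded share in the no-OAC group at r = 0.03:

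| Record length | Coded patients start OACs | Period 1 | Period 2 | Period 3 |
|---|---|---|---|---|
| All records from 1995 | at the same rate | 30.0% | 40.1% | 48.4% |
| All records from 1995 | twice as fast | 26.8% | 35.2% | 42.7% |
| Unrelated to calendar time | at the same rate | 34.3% | 33.6% | 32.8% |
| Unrelated to calendar time | twice as fast | 30.4% | 28.3% | 27.5% |

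Mean look-back in the first row is 12, 17 and 22 years. In the third it is 15.2, 14.9 and 14.5 years. The trend follows the record-length distribution.

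**4. Between groups within a period.** Untreated patients are read at the period end and starters at their index date. With 10 years of record at the period end and starts spread evenly over 5 years, the shares are 25.9% (no OAC) and 20.1% (OAC) from the end dates alone.

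**5. With a common window.** At the same constant rate, a 3-year window gives 8.6% and a 1-year window 3.0%, in every period and group.

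**The case against.** Several points on the other side stand.

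- A reader might infer that prevalence must rise from period to period by construction. The article does not support that. New diagnoses, 75th birthdays and new registrants enter the cohort, and patients leave the comparison once treated. Under one plausible record structure the share is flat or falls.
- A reader might also infer that both risk scores must rise. Age and sex points do not depend on look-back. The HAS-BLED point for antiplatelets or anti-inflammatory drugs depends on a prescription within the period, so it can be lost.
- In a patient carried through all periods, later codes are mostly real events in someone who is ageing. Capturing them is the stated purpose of re-reading covariates.
- Ever-history is a sensible definition for chronic disease and old strokes. A 12-month window on the three-supportive-codes rule could miss a stable patient with one review a year.
- Objective 3's formal contrast is within period, and no between-period test of characteristics is planned.
- The 12-month minimum concerns research-standard data, whereas the comorbidity rule searches the patient record. How far back records reach is not stated.

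Two replies remain. The Abstract, the strengths list and the Discussion all invite a reading over time, and differences in look-back also affect the within-period contrast. An article may leave supporting analyses to the full protocol, but the unlimited look-back is a rule this article states. Its discussion of limitations covers under-recorded comorbidities but not look-back length.

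**Conclusion.** The point holds in a limited form. Look-back is open-ended and unequal, and may lengthen over the three periods. For falls, previous bleeds, fractures and acute kidney injury counts, this can produce apparent differences between periods or groups that come from record length, and nothing in the article measures or corrects it.

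Neither size nor direction can be fixed from the article. At an assumed 3% per year, the untreated group's share moves from +18.4 percentage points (30.0% to 48.4%) to −1.5 points (34.3% to 32.8%) between the first and last period, depending only on the assumed record structure. All of these figures rest on assumed rates and record starts. That the direction is unknown is a reason to report look-back, not evidence of bias in a particular direction. The main definitions of chronic diagnoses and of the two risk scores need not change.

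**What to change.** Keep codes at any time before the reference date as the main definition, including for chronic diagnoses, the three-supportive-codes rule, CHA₂DS₂-VASc and HAS-BLED. Then add:

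1. A supporting analysis of falls, previous bleeds, fractures and acute kidney injury with one fixed look-back, chosen in advance and identical in all periods and groups. It could be 3 years among patients with at least 3 years of research-standard data before the reference date, or the guaranteed 12 months.
2. Median look-back by period and group.
3. A sentence stating that between-period statements about these four items will rest on the fixed-window figures.

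This needs one date filter and one table, and no new data. The 12-month window keeps every patient but misses older events. The 3-year window catches more events but drops patients with short records, so the number lost should be shown by period and group.
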